## Abstract

**Background:**

Esophagectomy with extended lymphadenectomy remains the mainstay of treatment for localized esophageal cancer. Currently, transthoracic and abdominal esophagectomy with cervical anastomosis (McKeown esophagectomy) is a frequently used technique in Japan. However, cervical anastomosis is still an invasive procedure with a high incidence of anastomotic leakage. The use of a drainage tube to treat anastomotic leakage is effective, but the routine placement of a closed suction drain around the anastomosis at the end of the operation remains controversial. The objective of this study is to evaluate the postoperative anastomotic leakage rate, duration to oral intake, hospital stay, and analgesic use with nonplacement of a cervical drainage tube as an alternative to placement of a cervical drainage tube.

**Methods:**

This is an investigator-initiated, investigator-driven, open-label, randomized controlled parallel-group, noninferiority trial. All adult patients (aged ≥20 and ≤85 years) with histologically proven, surgically resectable (cT1–3 N0–3 M0) squamous cell carcinoma, adenosquamous cell carcinoma, or basaloid squamous cell carcinoma of the intrathoracic esophagus, and European Clinical Oncology Group performance status 0, 1, or 2 are assessed for eligibility. Patients (*n* = 110) with resectable esophageal cancer who provide informed consent in the outpatient clinic are randomized to either nonplacement of a cervical drainage tube (*n* = 55) or placement of a cervical drainage tube (*n* = 55).

The primary outcome is the percentage of Clavien–Dindo grade 2 or higher anastomotic leakage.

**Discussion:**

This is the first randomized controlled trial comparing nonplacement versus placement of a cervical drainage tube during McKeown esophagectomy with regards to the usefulness of a drain for anastomotic leakage. If our hypothesis is correct, nonplacement of a cervical drainage tube will be recommended because it is associated with a similar anastomotic leakage rate but less pain than placement of a cervical drainage tube.

**Trial registration:**

UMIN-CTR, 000031244. Registered on 1 May 2018.

## Background

Torek described the world’s first case of transthoracic esophagectomy in 1913 [1]. Esophagectomy was performed via the left thoracic cavity without anastomosis. The meal passed from the stoma of the proximal esophagus through an external tube to the gastrostomy. Esophagectomy with extended lymphadenectomy has remained the mainstay of treatment for localized esophageal cancer [2–4]. Esophagectomy currently involves two surgical anastomoses: the McKeown approach (cervical anastomosis) [5] and the Ivor Lewis approach (intrathoracic anastomosis). Currently, transthoracic and abdominal esophagectomy with cervical anastomosis (McKeown esophagectomy) is the more commonly used technique in Japan. However, cervical anastomosis is still an invasive approach with a high incidence of anastomotic leakage [6–8]. The use of a drainage tube as treatment for anastomotic leakage is effective [9], but the efficacy of routinely placing a closed suction drain around the anastomosis at the end of the operation remains controversial. To date, there have been few prospective randomized controlled trials comparing nonplacement versus placement of a cervical drainage tube during McKeown esophagectomy. Choi et al. reported a randomized trial to evaluate the role of a drainage tube for the esophageal cervical anastomosis in 40 patients. They concluded that routine use of a neck drain for esophageal anastomosis in the neck is not necessary as there were no anastomotic leaks, seromas or hematomas in either group [10]. However, the number of patients in their study was too small to evaluate the usefulness of a drain for anastomotic leakage. Additionally, a cervical drainage tube might lead to respiratory complications including pneumothorax if it were placed from the neck into the thorax [11].

We present the protocol for the randomized controlled trial comparing these two surgical treatments.

## Methods/design

### Study aim

This is a randomized controlled, parallel-group, noninferiority trial of nonplacement versus placement of a cervical drainage tube in patients who undergo McKeown esophagectomy for indication.

### Objectives

Patients with resectable esophageal cancer are randomized in the outpatient clinic to either the nonplacement or placement group. The objective is to evaluate the safety and efficacy of nonplacement of a cervical drainage tube as an alternative to predictive placement of a cervical drainage tube as treatment for anastomosis leakage in McKeown esophagectomy. We hypothesize that nonplacement of a cervical drainage tube leads to a noninferior postoperative anastomotic leakage rate, duration to oral intake, hospital stay, and less analgesic use compared with placement of a cervical drainage tube, which is the current standard of care.

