#### Secondary outcomes

The duration from surgery to oral intake, hospital stay, and type and dose of analgesics used during hospitalization will be assessed.

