### Sample size calculation

Based on data from our own case series, the rate of Clavien–Dindo grade 2 or higher anastomosis leakage is 5%. Noninferiority is defined as a significant difference in the primary outcome between the two arms of less than 12%. Based on a one-sided type 1 error rate of 2.5% and power of 80%, the sample size needed to exclude a noninferiority margin of 12% for the difference in the proportion of participants reaching the primary outcome is 104 patients. An estimated compensation of 5% for withdrawals was added, resulting in a total of 110 patients, with 55 in each arm. Figure 1 summarizes the final study design.

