### Statistical analysis

All prospective data will be statistically analyzed using JMP® 11 (SAS Institute Inc., Cary, NC, USA). To evaluate the significance of differences between the two groups, Chi-squared and Fisher’s exact tests will be used as appropriate for categorical variables, and the nonparametric Mann–Whitney *U* test will be used for continuous variables. The significance level will be set at 5%.

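### Noninferiority is hypothesized for time to oral intake and hospital stay, but the only margin is for leakage and the only planned test for these two outcomes is a test of difference

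*Protocol article*

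**What the plan says.** All references are to the protocol article.

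- **Objectives.** The hypothesis is that "nonplacement of a cervical drainage tube leads to a noninferior postoperative anastomotic leakage rate, duration to oral intake, hospital stay, and less analgesic use" will result, compared with placement. The word noninferior governs the first three items, and the wording changes only for analgesic use.
- **Secondary outcomes.** "The duration from surgery to oral intake, hospital stay, and type and dose of analgesics used during hospitalization will be assessed". No margin is given.
- **Sample size calculation.** "Noninferiority is defined as a significant difference in the primary outcome between the two arms of less than 12" per cent. This is the only definition of noninferiority and the only margin in the document, and it is tied to the primary outcome.
- **Statistical analysis.** The tests are there to assess whether the groups differ. For continuous data, "the nonparametric Mann–Whitney *U* test will be used for continuous variables. The significance level will be set at 5" per cent. Sidedness is not stated.

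**The concern.** The null hypothesis of the Mann–Whitney test is that the two distributions are equal. Rejecting it shows a difference. Not rejecting it shows neither equality nor that one arm is no worse than the other by some stated amount. A noninferiority claim needs a stated amount and a confidence limit, or an equivalent test, set against it. For oral intake and hospital stay the article gives neither.

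The authors hypothesize noninferiority rather than superiority for these outcomes. If the arms are indeed about equal, the planned analysis will usually return p ≥ 0.05 and nothing else that bears on the claim. The risk is that this p-value is then reported as noninferior or similar. A smaller or noisier trial makes that more likely, and a real delay in oral intake or a longer stay could be reported as absent.

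The point is separate from how leakage is tested: repairing that analysis would still leave these two outcomes without a margin.

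**Working it through.** **1. The plan's own figure.** Inputs from the Sample size calculation: "the rate of Clavien–Dindo grade 2 or higher anastomosis leakage is 5" per cent (taken as equal in both arms), margin 12%, and "Based on a one-sided type 1 error rate of 2.5% and power of 80" per cent.

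n per arm = (1.960 + 0.842)² × 2 × 0.05 × 0.95 / 0.12² = 7.849 × 0.095 / 0.0144 = 51.8, so 52 per arm and 104 in total. Allowing for withdrawals, 104 / 0.95 = 109.5, so 110, or 55 per arm. The stated 104 and 110 are reproduced. They were derived from the leakage rate alone; oral intake and stay played no part.

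**2. What a non-significant Mann–Whitney result can hide.** The document gives no SD, expected value or relevant delay for either outcome, so the true worsening d is an assumption, expressed in SD units. Further assumptions are normal data (or data normal on some scale, such as log days, with d on that scale) and a two-sided 5% test. The relative efficiency of the Mann–Whitney test against the t-test is then 3/π = 0.955, and

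chance of non-significance ≈ 1 − Φ( d × √(0.955 n / 2) − 1.960 ).

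For n = 52, √(0.955 × 52 / 2) = 4.98. With d = 0.5 this gives 2.49 − 1.96 = 0.53, and 1 − Φ(0.53) = 0.298. For n = 55 the root is 5.12 and the result is 0.274.

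| True worsening | 52 per arm | 55 per arm |
|---|---|---|
| 0.3 SD | 67.9% | 66.4% |
| 0.4 SD | 48.7% | 46.4% |
| 0.5 SD | 29.8% | 27.4% |
| 0.6 SD | 15.2% | 13.2% |
| 0.7 SD | 6.3% | 5.2% |

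Simulating the test itself (20,000 replicates, normal data, 0.5 SD) gave 30.3% at 52 and 28.1% at 55 per arm. A second simulation gave 30.8% and 28.9%.

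**3. Sensitivity to skewness.** For log-normal data (log-SD 0.5) with one arm shifted by 0.5 of the raw SD, the simulated rate falls to 13.1% at 52 and 10.8% at 55 per arm. The size of the problem therefore depends on the assumed shift and on the shape of the data.

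**4. Comparison with a real noninferiority test.** Take an illustrative margin of 0.5 SD, one-sided 2.5%, 80% power and a true difference of zero. Then n = 2 × 7.849 / 0.5² = 62.8, so 63 per arm. With 52 or 55 per arm the margin that can be excluded at 80% power is 2.802 × √(2/52) = 0.55 SD or 2.802 × √(2/55) = 0.53 SD. Such a test would wrongly declare noninferiority in 2.5% of trials when the true worsening equals the margin. Reading non-significance as noninferiority would do so in about 29% at 0.5 SD (normal data).

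**The case against.** **The wording.** The claim for stay and oral intake rests on one loosely built sentence. The Abstract speaks only of evaluating these outcomes, the Secondary outcomes section of assessing them, and the Discussion restates the noninferiority hypothesis for leakage alone. This suggests that leakage was meant to be the only noninferiority endpoint. It does not remove the mismatch, because the Objectives sentence is where the hypothesis is set out in full and its natural reading covers all three outcomes. It does make the repair simple.

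**The recommendation.** A reader might infer that a non-significant result for stay or oral intake would help trigger the recommendation for nonplacement, since that recommendation is conditional on the hypothesis being correct. The documents do not support this. The Abstract's discussion and the Conclusions give similar leakage and less pain as the grounds, the main Discussion argues in the same way, and none of them relies on stay or oral intake.

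**Non-significance as the only route.** A reader might also infer that the claim can rest on nothing but p ≥ 0.05. That goes too far: a significant result favouring nonplacement would also support noninferiority. Nor does the article say that p ≥ 0.05 will be read as noninferior, or rule out confidence intervals.

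**Matters for the SAP.** Estimators and intervals for secondary outcomes are commonly left to an analysis plan that is not shown, and their absence alone would be no finding. What stands is narrower: the article itself pairs a noninferiority hypothesis with a difference test for the same outcomes.

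**Conclusion.** The point holds for the two secondary outcomes. The article hypothesizes noninferior time to oral intake and hospital stay, sets a margin for leakage only, and fixes an analysis that cannot show noninferiority unless nonplacement turns out significantly better.

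The figures of about 68%, 48% and 29% for a worsening of 0.3, 0.4 and 0.5 SD illustrate the size. They rest on assumed shifts, normal data, a two-sided test and 52 to 55 per arm. Across shifts of 0.3 to 0.7 SD the range is roughly 68% down to 5–6%, and a 0.5 SD shift in the skewed example gives 11–13%. No one of these percentages should be taken as a property of this trial. The mismatch between hypothesis and test does not depend on them.

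The effect is on what may be claimed about oral intake and stay. The main conclusion, which rests on leakage and pain, is not touched by this point.

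**What to change.** 1. In Objectives, limit the noninferiority wording to the leakage rate, and say that time to oral intake and hospital stay will be compared by estimation.
2. In Statistical analysis, report for each of these two outcomes the difference in days, nonplacement minus placement (for example the Hodges–Lehmann estimate), with a two-sided 95% CI. State that a non-significant Mann–Whitney test will not be read as noninferior or similar.
3. If a noninferiority claim is to be kept for either outcome, fix a justified margin in days before database lock, and make the claim only if the upper 95% limit lies below it. The trial is open-label, so a margin chosen once results are known would carry little weight.

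The cost is a change of wording and two confidence intervals from data already being collected, with no extra patients. The downside is that the trial gives up the noninferiority claim for two secondary outcomes, or must earn it against a margin for which it was not sized.

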### Study design

This is an investigator-initiated, investigator-driven, open-label, randomized controlled, parallel-group, noninferiority trial comparing nonplacement versus placement of a cervical drainage tube during esophagectomy with cervical anastomosis.

This study will be conducted in compliance with the Declaration of Helsinki [12] and the Kobe University Conflicts of Interest Management Guidelines. Written informed consent will be obtained from all participating patients. The principal investigator will appoint responsible monitors for this study. The appointed monitors must have received training on the Ethical Guidelines for Medical and Health Research involving Human Subjects and other regulatory requirements and be thoroughly familiar with the contents of the study protocol, informed consent form, and written monitoring procedures.

### Study population

The diagnosis of esophageal cancer was based on the seventh edition of the Union for International Cancer Control tumor node metastasis cancer staging system [13]. All Japanese adult patients (aged ≥20 and ≤85 years) with histologically proven, surgically resectable (cT1–3 N0–3 M0) squamous cell carcinoma, adenosquamous cell carcinoma, or basaloid squamous cell carcinoma of the intrathoracic esophagus will be assessed for eligibility. Patients should have European Clinical Oncology Group performance status of 0, 1, or 2.

The inclusion criteria are:
Histologically proven squamous cell carcinoma, adenosquamous cell carcinoma, or basaloid squamous cell carcinoma of the intrathoracic esophagusSurgically resectable disease (T1–3 N0–3 M0)Age ≥20 and ≤85 yearsEuropean Clinical Oncology Group performance status of 0, 1, or 2Written informed consent

The exclusion criteria are:
Carcinoma of the cervical esophagusCarcinoma of the gastroesophageal junction with the majority of the tumor in the gastric cardiaSevere systemic infectionPregnancyMental illnessSystemic steroid or immunosuppressive therapy

### Study protocol

Patients are informed about the trial by one of our surgeons [name] in the Surgical Oncology outpatient clinic. After receiving information about the trial, all patients have 2 weeks to consider whether to participate. After 2 weeks, the coordinating researcher [name] contacts the patient to see if they would like to make an appointment to provide informed consent. After obtaining informed consent, randomization is performed using a computerized random number generator by a researcher [name] on the eve of the operation. Concealment of allocation is maintained by using sealed opaque envelopes. There is no blinding for the patient, surgeon, or coordinating researcher after the operation because this is difficult in daily practice. After the operation, patients are informed about the allocated treatment. This study is completely funded by the Division of Gastrointestinal Surgery of Kobe University. The patient’s clinical status is assessed, and preoperative testing is performed.

Next, patients undergo the randomized intervention with either nonplacement or placement of a cervical drainage tube. The study began on 26 July 2018. Each patient undergoes follow-up at 2 weeks after surgery to assess primary and secondary outcomes (Table 1).

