### Criteria for discontinuation

When a participant’s continuation in the study is judged to be impossible (see below for possible reasons), the principal investigator or subinvestigator will withdraw the participant from the study and specify the date and time of the discontinuation or dropout, the reason for discontinuation or dropout, and the clinical course in the medical record and case report form (CRF). In addition, at the time of the discontinuation/dropout, the principal investigator or subinvestigator will perform necessary tests and assess the efficacy and safety.

Reasons for discontinuation or dropout include:
When the participant requests to withdraw from the study or withdraws consentWhen the participant is found not to meet the eligibility criteria after enrollmentWhen a concurrent disease worsens and further continuation with the study is difficultWhen an adverse event occurs and further continuation with the study is difficultWhen discontinuation from the study is appropriate for other reasons in the opinion of the principal investigator or subinvestigator

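### The protocol gives two times for randomization, both before surgery, and nothing keeps the arm from the surgeon until the anastomosis is finished

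*Protocol article*

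**What the plan says.** Two sections of the protocol article give different times for randomization.

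- Objectives: "Patients with resectable esophageal cancer are randomized in the outpatient clinic to either the nonplacement or placement group".
- Study protocol: after consent, "randomization is performed using a computerized random number generator by a researcher", and this is done "on the eve of the operation. Concealment of allocation is maintained by using sealed opaque envelopes".

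The abstract refers to patients "who provide informed consent in the outpatient clinic are randomized to either nonplacement of a cervical drainage tube". That sentence can be read as placing only the consent in the clinic, so it need not conflict with the Study protocol section.

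On blinding, the Study protocol section says: "There is no blinding for the patient, surgeon, or coordinating researcher after the operation because this is difficult in daily practice". It adds: "After the operation, patients are informed about the allocated treatment". Nothing equivalent is said about when the surgeon learns the arm. The Study design section calls the trial open-label.

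The surgical sections describe making the esophagogastric anastomosis in the neck and, in the placement group, putting the tip of a drain near it. The primary outcome is anastomotic leakage of Clavien–Dindo grade 2 or higher.

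The Criteria for discontinuation section allows withdrawal for several reasons. They include worsening disease, an adverse event, the investigator's opinion, and the case where a "participant is found not to meet the eligibility criteria after" enrollment. It also requires efficacy and safety to be assessed at that point. The Sample size calculation section states: "An estimated compensation of 5% for withdrawals was added".

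**The concern.** The two arms are treated identically until the anastomosis exists. Fixing the arm in the clinic or the evening before therefore allocates earlier than the comparison needs, and it opens two routes to bias.

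The first is technique. A surgeon who knows that no drain will follow may build or reinforce the anastomosis differently. The trial would then compare drain plus technique rather than the drain alone. Extra care in the nonplacement arm would push the result toward noninferiority.

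The second is loss after allocation. Surgically resectable disease is an inclusion criterion, so a patient found unresectable at operation would be ineligible after having been allocated. If the arm is known by then, decisions about who stays in the trial are no longer independent of it.

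**Working it through.** **1. The passages side by side**

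| Question | Objectives | Study protocol |
|---|---|---|
| When or where is the patient randomized? | Outpatient clinic | Evening before surgery, after consent |
| When is the envelope opened? | Not stated | Not stated |
| When does the patient learn the arm? | Not stated | After the operation |
| When does the surgeon learn the arm? | Not stated | Not stated; unblinded afterwards |

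The first row is a contradiction. The other rows show that neither section separates knowledge of the arm from construction of the anastomosis. The surgeon must know the arm by the time the drain is or is not placed, and no text sets how much earlier that may be.

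**2. The plan's own sample size**

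Inputs from the Sample size calculation section: 5% leakage (taken as equal in both arms), margin 0.12, one-sided alpha 0.025, power 80%.

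n per arm = 2 × 0.05 × 0.95 × (1.960 + 0.842)² / 0.12² = 51.8, rounded up to 52, giving 104 in total. Then 104 / 0.95 = 109.5, rounded up to 110. Both stated figures reproduce, and neither depends on when the envelope is opened.

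**3. Scale of the event count**

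Expected primary events are 110 × 0.05 = 5.5. The withdrawal allowance is 110 − 104 = 6 patients, about as many as all expected events.

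**4. How close the decision is, at 55 per arm with 3 control leaks**

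Newcombe upper limit = d + √[(u₁ − p₁)² + (p₂ − l₂)²], where l and u are Wilson 95% limits, arm 1 is nonplacement and d = p₁ − p₂. For 3/55, p = 0.0545, l = 0.0187 and u = 0.1485. For 4/55, p = 0.0727 and u = 0.1726.

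Wald upper limit = d + 1.96 × √[p₁(1 − p₁)/55 + p₂(1 − p₂)/55].

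| Leaks, nonplacement v placement | Newcombe upper limit | Wald upper limit |
|---|---|---|
| 3 v 3 | 10.1 points (pass) | 8.5 points (pass) |
| 4 v 3 | 12.4 points (fail) | 10.9 points (pass) |
| 5 v 3 | 14.7 points (fail) | 13.3 points (fail) |

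A Miettinen–Nurminen score test agrees with Newcombe (z = −2.22 at 3 v 3 and −1.86 at 4 v 3, against −1.96). The protocol article names no interval method, and its sample size rests on the unpooled normal approximation that underlies Wald.

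**5. Withdrawal of leak patients (illustration only)**

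Assume a fraction w of leak patients in both arms leaves with no outcome counted. The document gives no value for w. The observed rate is p(1 − w)/(1 − pw). Start from a true 17% v 5%, which is exactly the 12-point margin. False noninferiority is the summed probability of all pairs of binomial counts at 55 per arm that pass.

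| w | Apparent rates | Apparent excess | False noninferiority, Newcombe | Wald |
|---|---|---|---|---|
| 0% | 17.0% v 5.0% | 12.0 points | 2.3% | 3.3% |
| 10% | 15.6% v 4.5% | 11.0 points | 3.3% | 4.8% |
| 20% | 14.1% v 4.0% | 10.0 points | 4.8% | 7.2% |
| 30% | 12.5% v 3.6% | 9.0 points | 6.9% | 11.0% |

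These are withdrawals after surgery. Opening the envelope later would prevent none of them.

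**6. Loss of precision if losses exceed 5%**

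Power = Φ(0.12 / √(2 × 0.05 × 0.95 / n) − 1.96). This gives 80.2% at 52 per arm (5% loss). At assumed losses of 10%, 15% and 20% (49, 46 and 44 per arm) it gives 77.8%, 75.2% and 73.3%.

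**The case against.** The strongest reply is that surgeon awareness is inferred. Opaque envelopes, unblinding described only for the period after surgery, and patients told afterwards can together be read as concealment up to the operation. Generating an allocation the evening before does not show that anyone saw it. A condensed article may also leave the opening time to the full protocol. This stands as far as it goes: a reader might infer that the surgeon knows the arm while operating, and the document does not say so. But the timing the article does state is contradictory, and both versions put allocation before an open-label operation.

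On withdrawals, the discontinuation section requires an efficacy and safety assessment at dropout, so a leak that prompted withdrawal should already be recorded. The section does not say that such patients leave the analysis, and analysis sets may properly sit in a statistical analysis plan not shown here. That also stands. What remains open is a leak that appears after an early dropout but before the 2-week visit.

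On magnitude, the one-event change of conclusion depends on the interval method, and the fragility comes from few events and 55 patients per arm whenever the envelope is opened. The 20% withdrawal figure has no source in the document. All of this is accepted.

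**Conclusion.** The point holds as a design weakness. The Objectives and Study protocol sections contradict each other on when patients are randomized. Under either, allocation comes before the step that determines the primary outcome, with no stated safeguard that keeps the arm from the surgeon during it.

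Three stronger readings are not supported. The document does not show that the surgeon knows the arm. Later opening would not remove every bias, because withdrawals after opening remain possible. Nor does the document support a figure for false noninferiority: no input measures the effect on technique, and the withdrawal table rests wholly on an assumed w.

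The size of the bias is therefore unknown. What can be said is that about 5.5 events are expected. With 3 control leaks, moving from 3 to 4 nonplacement leaks reverses the conclusion under Newcombe or score limits; under Wald limits it takes 5. The sample size of 104, raised to 110, is unaffected.

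**What to change.** Keep information and consent in the clinic. Allocate by opening the next sealed opaque envelope in theatre, only after the cervical anastomosis is complete and eligibility has been confirmed, and record the time of opening. Amend the Objectives and Study protocol sections to say this in the same terms. The abstract can stand if its clinic reference is meant for consent. Anastomotic technique is then independent of the arm, and exclusions made during the operation come before allocation. Delaying only the opening, with randomization left on the evening before, would protect technique but would still count those exclusions as losses after randomization.

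In the Criteria for discontinuation section, add that discontinuation does not end ascertainment of leakage at 2 weeks, unless the patient withdraws consent to follow-up.

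The cost is protocol wording and the small logistic burden of holding envelopes in theatre. No change to the sample size is needed. Recruitment has started according to the Trial status section, so the date of the change should be recorded, along with the opening time for patients already allocated where it is known.
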